## Abstract

Background: Exercise training has positive effects on physical functions and could reduce a sedentary lifestyle for hemodialysis (HD) patients. Given that low-level physical activity increases morbidity and mortality, here, we aimed to determine the effects of an intradialytic exercise program delivered at different frequencies on HD patients in Taiwan. Methods: This study is a prospective, randomized control trial. An intradialytic exercise program will be arranged for patients after receiving their informed consent. Patients will be segregated at random into three groups as follows: (a) three times/week of intradialytic exercise training plus standard care maintenance of HD, (b) two times/week of intradialytic exercise training plus standard care maintenance of HD, or (c) standard care maintenance of HD. Subjects will be followed for 24 weeks. At three time points, 0, 12, and 24 weeks, the primary outcome, the Short-Form 36 score, will be measured. Additional secondary outcomes to be measured are the Beck depression inventory, 6 min walking test, sit-to-stand test, and anthropometric measures such as the body mass index, thigh circumference, and the proportion of fat in the body composition. Conclusions: There is emerging evidence in support of intradialytic exercise improving health-related quality of life for patients on HD. However, the difference in the therapeutic effects between three times per week and twice per week has never been determined. With this study, we anticipate to fill the knowledge gap in the exercise prescription among HD patients.

## 1. Introduction

Patients with chronic kidney disease (CKD) constitute a large portion of the population in modern society. They cause a tremendous amount of medical expenditure. In the United States, ≥30 million adults (~14.8% of the adult population) have CKD [1]. These patients rely on either maintenance dialysis or a renal transplant, as CKD progresses to end-stage renal disease (ESRD). In Taiwan, the prevalence of hemodialysis (HD) ranks top in the world; 15–30% higher in the HD rate compared with the United States. In Taiwan, the national prevalence of hemodialysis is 3587 per million people, and ~94,000 patients undergo HD every year. The number of HD increases by 3% to 4% annually [2]. HD is a lengthy process repeating two to three times per week, with each session lasting 3 to 4 h.

There is good evidence that a low level of physical activity is associated with increased morbidity and mortality [3,4,5,6]. Those patients classified as stage 5 CKD typically have a low functional capacity, which is about only 50–80% of their sex- and age-matched controls [7]. Patients on HD have higher rates of falls, hospitalization, morbidity, and mortality [8]. Exercise training in CKD patients can lead to a blood pressure reduction and improvement in aerobic capacity, heart rate variability, muscular function, and health-related quality of life (HRQoL) [9]. Given the benefits of exercise training, the American College of Sports Medicine (ACSM) guidelines recommend that CKD patients, including those with ESRD, should gradually progress from low-intensity exercise of 10–15 min in duration to a greater volume of exercise [10]. Intradialytic exercise is engaged with the use of pedaling and stepping devices, while a patient is seated in a dialysis chair. In the United Kingdom (UK), structured exercise interventions, mostly delivered by a cycle ergometer during HD at medical centers, have shown clinical benefits in patients. These were also shown to improve HD adequacy, have anti-depressive effects, cost-effective outcomes, and improve quality of life in these British patients [11,12].

Despite the benefits aforementioned, the intradialytic exercise program is not commonly incorporated into regular HD care worldwide. After all, the formal recommendation from the ACSM is to perform exercise training for a minimum of two hours after, but not during, HD [10]. In Taiwan, no HD unit incorporates an exercise program as part of regular care. Very few studies have evaluated the effects of structured intradialytic exercise programs on the level of physical activity and HRQoL of HD patients [13,14,15]. According to the ACSM’s guideline for an exercise prescription [10], the frequency of aerobic exercise for HD patients is 3 to 5 days per week. Whether a low frequency of exercise (such as two days per week) produces similar therapeutic effects is unclear. The objective of this randomized control trial is, therefore, to compare the efficacy of different frequencies of structured intradialytic exercise programs on Asian HD patients in Taiwan.

## 2. Materials and Methods

### 2.1. Study Design Overview

This study is a randomized control trial in which participants will be grouped into 3 regular maintenance dialysis groups, with intradialytic exercise given (a) twice per week and (b) three times per week. The outcome measures will be measured at 3 time points: (a) right after the recruitment of participants, and after the initiation of the study, (b) 3 months later, and (c) 6 months later. The timings of the outcome measurements will be set according to past studies on intradialytic exercise. Some of them measured the results after 3 months of intradialytic exercise [13,14,15], while others were evaluated 6 months later [11,16].

### 2.2. Study Participants

#### 2.2.1. Selection Criteria

Patients receiving HD in a tertiary medical center in Taiwan will be screened for eligibility. Participants must be ≥18 years old and have received HD treatments without adverse events for ≥90 days. Considering that different baseline exercise habits may pose a significant confounding factor in this study, having no previous regular exercise habits is also listed to be one of our inclusion criteria. The exclusion criteria include: patients with an expected survival of ≤6 months, patients being withdrawn from HD within 6 months (such as those likely to receive a kidney transplantation or transfer to peritoneal dialysis), a Charlson comorbidity index (CCI) of >10, lower-limb amputations, or conditions such as dementia and/or psychiatric disorders that would not allow patients to complete the outcome measures of this study.

#### 2.2.2. Randomization

After signing informed consent, participants will be randomly divided into three groups: (i) 3 times/week of intradialytic exercise training plus usual care maintenance of HD, (ii) 2 times/week of intradialytic exercise training plus usual care maintenance of HD, and (iii) usual care maintenance of HD. Randomization of the allocation sequence will be completed using computer-generated random numbers, while taking age, gender, and diabetes status into consideration. A project assistant will examine the outcome measures, and both the participants and the assistant will not be blindly involved in this study.

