### 2.4. Data Collection and Outcomes

Data will be collected according to the study timeline as displayed in Figure 1. Clinical data, which include blood pressure, heart rate, and body weight, will be obtained before and after the routine care protocols of HD from electronic health records. Adverse events such as hypotensive episodes, cramping, nausea, vomiting, or loss of consciousness will be monitored by clinical personnel. Results of the baseline laboratory tests (e.g. electrolytes, albumin, complete blood count, and dialysis efficiency using Kt/V) will also be extracted from the electronic health records.

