#### 2.4.1. Primary Outcomes

Our primary outcome measure of patients is the Short-Form 36 (SF-36) questionnaire, which evaluates the health-related quality of life of the participants. The validity and reliability of the Chinese version of this questionnaire were confirmed in a previous study [17]. Patients who are illiterate or have visual problems will be provided verbal assistance when completing the questionnaire. The SF-36 questionnaire includes 8 subdomains, namely, vitality, physical function, bodily pain, general health perception, physical role functioning, emotional role functioning, social role functioning, and mental health. The lower the score, the lower the self-rated quality of life. These 8 subdomains are integrated into two domains: the physical component scale (PCS) and the mental component scale (MCS).

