#### 2.4.2. Secondary Outcomes

Secondary outcome measures include the Beck depression inventory (BDI) to evaluate the status of depression, 6 min walking test (6MWT) to determine cardiopulmonary endurance, sit-to-stand test (STS-30) to measure lower-limb muscle endurance, and anthropometric measures, such as body mass index (BMI), thigh circumference, and the fat proportion in the body composition as obtained from the bioimpedance analysis (Tanita MC-780).

A 21-item, self-rated BDI with good reported validity and reliability will be applied to measure the depression status of the participants [18,19]. This BDI includes symptoms of depression such as hopelessness and irritability, cognitions such as guilt or feelings of being punished, as well as physical symptoms such as fatigue, weight loss, and lack of interest in sex. Subjects will rate each question on a 4-point scale. The severity of depression is represented by the summed score that ranges from 0 to 63. Scores of 0–13 indicate minimal depression, 14–19 indicate mild depression, 20–28 indicate moderate depression, and 29–63 indicate severe or major depression.

Physical function such as cardiopulmonary endurance will be assessed with 6MWT, and the muscle endurance of lower limbs will be assessed with STS-30. 6MWT is a self-paced test of walking capacity to reflect the functional ability of daily activities [20]. Participants will walk along a walkway (30 m long, 2 m wide) in a quiet corridor of the hospital. Markers will be placed on the walkway at 5 m intervals. Participants will be instructed to walk as far as they can within a period of 6 min, but are allowed to stop and rest if necessary. STS-30 is an indirect measure of lower-limb muscle strength and endurance [21]. Using a chair without arms placed against the wall to maintain stability, the seat height will be adjusted to allow the thigh to be parallel to the ground. The STS-30 test measures the repeated number of times a patient can stand up and sit down from a chair repeatedly during a 30 s period while their arms are crossed in front of their chest.

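### The protocol leaves the outcome assistant unblinded without need, which exposes the two effort-dependent performance tests (6MWT and STS-30) to examiner bias

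*Protocol article*

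**What the plan says.** On masking, section 2.2.2 (Randomization) of the protocol article says: "A project assistant will examine the outcome measures, and both the participants and the assistant will not be blindly involved in this study". The phrasing is awkward, but the only sensible meaning is that neither the patients nor the assistant is blinded. No reason is given for the assistant.

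Section 2.4.2 (Secondary Outcomes) describes the two performance tests. On the walk: "6MWT is a self-paced test of walking capacity to reflect the functional ability of daily activities", and "Participants will be instructed to walk as far as they can within a period of 6 min", with rests permitted. On the chair stand: "The STS-30 test measures the repeated number of times a patient can stand up and sit down from a chair repeatedly during a 30 s".

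Section 2.4.1 (Primary Outcomes) makes the SF-36 questionnaire primary and adds: "Patients who are illiterate or have visual problems will be provided verbal assistance when completing the questionnaire". It does not say who gives that help.

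Section 2.5 compares improvements between the three groups by ANOVA or Kruskal–Wallis.

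**The concern.** In an exercise trial the participants cannot be blinded. The examiner usually can be, and here the article positively fixes the opposite. This is a stated choice, not a detail left to a fuller document.

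The choice matters most for the 6MWT and STS-30. The SF-36 and the BDI are answered by patients who know their arm, so the two performance tests are the natural check on an open-label, self-reported primary outcome. Their scores depend on how hard the patient tries, and an examiner who knows the arm can influence that without intending to. If so, the check loses much of its value. The trial's own question, whether two sessions a week do about as well as three, is also exposed: encouragement that differs by frequency could create or blur a gradient between the exercise arms. Bias recorded in a score cannot be removed by analysis.

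**Working it through.** **Inputs from section 2.5.** Total N = 84, alpha 0.05, power 0.80, effect size 0.35; between-group ANOVA on improvement.

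**Assumptions, not in the article.** Allocation 1:1:1, so n = 84/3 = 28 per arm; effect size read as Cohen's f; no true treatment effect; equal variances at baseline and follow-up; baseline to follow-up correlation r = 0.5, 0.6 or 0.7; unblinded examination raises follow-up scores by d SD in the exercise arms and not in usual care.

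**Step 1: the plan's own figure.** For a one-way three-group ANOVA, λ = f²N = 0.35² × 84 = 10.29 with 2 and 81 degrees of freedom. Power is 0.812, and 84 is the smallest multiple of 3 that reaches 0.80. This supports 84 as the basis for the check; masking the assessor would not change it.

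**Step 2: false-positive rate under an examiner shift.** In baseline SD units the variance of change is 2(1 − r), so

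λ = n Σ(μᵢ − μ̄)² / [2(1 − r)].

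For shifts (d, d, 0) the sum of squares is 2d²/3. For d = 0.2 and r = 0.5: λ = 28 × (2/3) × 0.04 / 1 = 0.747. For a graded shift (d, d/2, 0) the sum is d²/2. For d = 0.3 and r = 0.5: λ = 28 × 0.5 × 0.09 / 1 = 1.26. The rate is the probability that a noncentral F(2, 81, λ) exceeds the 5% critical value, 3.109.

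| Assumed shift (3x, 2x, usual care) | r = 0.5 | r = 0.6 | r = 0.7 |
|---|---|---|---|
| none | 0.050 | 0.050 | 0.050 |
| 0.1, 0.1, 0 | 0.064 | 0.067 | 0.073 |
| 0.2, 0.2, 0 | 0.108 | 0.124 | 0.151 |
| 0.3, 0.3, 0 | 0.189 | 0.228 | 0.293 |
| 0.3, 0.15, 0 | 0.152 | 0.180 | 0.228 |

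**Step 3: does the same size apply to the SF-36?** Step 2 shifts every patient in the exercise arms. For the SF-36 an assistant could reach only those who receive verbal help. If a share s is helped, the mean shift is s × d. The article gives no s, so a range is shown, for d = 0.2 to 0.3 and r = 0.5 to 0.7.

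| Assumed share helped | False-positive rate |
|---|---|
| 20% | 0.052 to 0.058 |
| 30% | 0.055 to 0.069 |
| 50% | 0.064 to 0.104 |

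So the 11% to 29% range can describe at most the two performance tests.

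**The case against.** The strongest reply has four parts.

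- **The size of the bias is assumed.** This stands. No figure in the article supports 0.2 or 0.3 SD, and at 0.1 SD the inflation is small. Patients also know their arm, so part of any shift would come from their own effort and expectation, which masking the examiner leaves untouched.
- **The tests are partly standardised.** Section 2.4.2 fixes the walkway, the markers, the instruction to the patient, the seat height, the arm position and the 30 s limit, and the scores are a distance and a count. This limits scoring error. It does not control encouragement during the test.
- **Masking may not be free.** A reader might infer that unit staff already run the exercise, so that no extra person is needed. Section 2.4 does not say so: it lists adverse events such as hypotensive episodes and ends "loss of consciousness will be monitored by clinical personnel". Section 2.3.2 has each session monitored without naming by whom. Equally, a reader might infer that the unblinded assistant both coaches and scores the tests. The article gives the assistant only the examination of outcomes and mentions no coaching. Who supervises the sessions has to be confirmed.
- **The primary outcome is self-reported.** A reader might infer that examiner bias reaches the SF-36 at the same size through verbal help. The article does not support this: only some patients are helped, the helper is not named, and the rate stays near 5% to 7% if 20% to 30% are helped. Bias from unblinded self-report would remain with a masked assistant.

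None of this gives a reason for the assistant to know the allocation.

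**Conclusion.** The point holds for the 6MWT and STS-30. Section 2.2.2 fixes an unblinded examiner without stated need, and these two secondary outcomes can respond to encouragement. Under the stated assumptions the false-positive rate of the ANOVA on change is 6% to 7% for a shift of 0.1 SD, 11% to 15% for 0.2 SD and 19% to 29% for 0.3 SD. A graded shift of 0.3 and 0.15 SD gives 15% to 23% and could pass for a frequency response. These figures show what such a bias could do; they do not estimate what it will do. No claim of that size is made for the SF-36. The change is worth making but does not decide whether the trial is valid, since the affected outcomes are secondary and the size of the bias is unknown.

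**What to change.** Replace the masking sentence in section 2.2.2. Participants remain unblinded. The existing assistant who examines outcomes should not supervise exercise sessions, should not see the allocation list, should test patients away from the dialysis station after asking them not to disclose their arm, and should record any unmasking. This is conditional on the sponsor confirming that the assistant is not needed to run the sessions.

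In any case, add to section 2.4.2 that the 6MWT and STS-30 use the same fixed scripted wording in all arms at 0, 12 and 24 weeks. If masking would need extra staff, keep the script and state the unblinded assessment as a limitation when these two tests are interpreted.

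The cost is protocol wording, the scheduling of tests away from the dialysis station, and some accidental unmasking. Sample size, outcomes, the timing of assessments and treatment stay as they are.

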### 2.3. Intervention

#### 2.3.1. Usual Care

All participants will receive HD as prescribed and will be adjusted by attending nephrologists. The HD routine care includes the management of blood pressure, the treatment of anemia, the control of electrolyte level, and mitigation strategies of cardiovascular risk. All participants will receive HD using the Fresenius 4008S machine. The participants will be encouraged to maintain their regular physical activities as usual, and no extra exercise training should commence during the 6 months of the follow-up period.

#### 2.3.2. Intradialytic Exercise

The intradialytic exercise program is based on the leading CYCLE-HD program from a study group in the United Kingdom [16]. Participants perform 30 min of continuous cycling at a 12 to 13 rating of perceived exertion (RPE) during HD for a total of 6 months. The cycling exercise is executed during the first 2 h of HD with participants lying in supine posture. Specially adapted and calibrated cycle ergometers (WINGS PLUS WP-948) are used for exercise training. Participants in the intradialytic exercise groups will receive cycling training either 2 or 3 times a week during HD. Resistance training for bilateral knee extensors using ankle weights will be incorporated after the aerobic cycling exercise for the participants. Exercise duration, intensity (RPE), blood pressure, and heart rate will be monitored for each exercise session. As in the usual care group, these participants will also be encouraged to keep their original daily activities without additional exercise training during the study period.

### 2.4. Data Collection and Outcomes

Data will be collected according to the study timeline as displayed in Figure 1. Clinical data, which include blood pressure, heart rate, and body weight, will be obtained before and after the routine care protocols of HD from electronic health records. Adverse events such as hypotensive episodes, cramping, nausea, vomiting, or loss of consciousness will be monitored by clinical personnel. Results of the baseline laboratory tests (e.g. electrolytes, albumin, complete blood count, and dialysis efficiency using Kt/V) will also be extracted from the electronic health records.

#### 2.4.1. Primary Outcomes

Our primary outcome measure of patients is the Short-Form 36 (SF-36) questionnaire, which evaluates the health-related quality of life of the participants. The validity and reliability of the Chinese version of this questionnaire were confirmed in a previous study [17]. Patients who are illiterate or have visual problems will be provided verbal assistance when completing the questionnaire. The SF-36 questionnaire includes 8 subdomains, namely, vitality, physical function, bodily pain, general health perception, physical role functioning, emotional role functioning, social role functioning, and mental health. The lower the score, the lower the self-rated quality of life. These 8 subdomains are integrated into two domains: the physical component scale (PCS) and the mental component scale (MCS).

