### 2.5. Statistical Analysis and Power Estimates

Statistical analyses will be performed using SPSS, version 22.0 (SPSS Inc., Chicago, IL, USA). The Shapiro–Wilk test of normality will be used to evaluate the distribution of each outcome variable. If data are normally distributed, paired t*tests and analysis of variance (ANOVA) will be used. If data are not normally distributed, the Wilcoxon signed-rank test and Kruskal–Wallis test will be used. The preintervention outcome measures will be compared using ANOVA or Kruskal–Wallis test. Paired t-tests or Wilcoxon signed-rank test will be applied to compare differences between pre- and post-tests. After the exercise intervention, intergroup comparisons regarding improvements of outcome measures will be determined using ANOVA or Kruskal–Wallis test.

The G*Power (Germany, version 3.1.9) software will be used for sample size estimation [22]. Based on repeated measures ANOVA, a statistical power of 0.8, a significant level of 0.05, the effect size is 0.35, refs. [23,24,25], and a minimum of 84 participants are required for our study. We noted the likelihood of a high drop-out rate for intradialytic exercise [26].

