Systematic reviews and meta-analyses found a significantly improved PCS in the intradialytic exercise group, but not in the MCS [32,35,36]. However, some subdomains of the MCS are still improved after intradialytic exercise. These subdomains include “limitations due to emotional problems” scores in an Iranian study [37], and “bodily pain” scores in a Korean study [38]. As mental problems constitute an important component of life quality, they should not be overlooked in HD patients. Compared with the US general population and US HD cohorts, Taiwanese HD patients have substantially lower physical and mental aspects of life quality [29]. It is well known that for HD patients, their poor physical dimension of HRQoL predicts higher mortality [39]. Therefore, our study will use the SF-36 score as our primary outcome measure, aiming to evaluate the effects of different frequencies of intradialytic exercise on HRQoL.

Blood pressure is regulated through various neural mechanisms involving the sympathetic nervous system, vasoconstriction, and baroreflex activity. During HD, a patient may experience acute hypotension, primarily due to hypovolemia and poor compensatory mechanisms to counter the reduced intravascular volume. In addition, autonomic dysfunction is highly prevalent in these patients, and it has been implicated in the increased risk of blood pressure instability during HD [40,41,42]. In the supine position, SBP is lower due to the reduced effect of gravity on blood in its return to the heart [43]. HD is typically conducted in either a lying or a seated position. While exercise-induced hypotension is of concern for patients and their healthcare givers, our study protocol involves intradialytic exercise in a supine posture, simply to minimize the exercise-induced hypotension.

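### The primary outcome is the whole SF-36, with no score or visit fixed, so several scores could each serve as the primary result of a trial sized for one test

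*Protocol article*

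**What the plan says.** Section 2.4.1 makes an instrument the primary outcome: "Our primary outcome measure of patients is the Short-Form 36 (SF-36) questionnaire, which evaluates the health-related quality of life of the participants". It then says "The SF-36 questionnaire includes 8 subdomains" and lists them, and continues: "These 8 subdomains are integrated into two domains: the physical component scale (PCS) and the mental component scale (MCS"). It describes no total score.

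Elsewhere the outcome is treated as one number. The abstract says "At three time points, 0, 12, and 24 weeks, the primary outcome, the Short-Form 36 score, will be measured", and the Discussion says "our study will use the SF-36 score as our primary outcome measure". Neither says which score is meant, and no section says whether week 12 or week 24 is primary.

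Section 2.5 plans ANOVA or Kruskal–Wallis to compare improvements between the three groups, and paired tests within groups. It ranks no score above another and gives no rule for combining them. The sample size of 84 rests on "a statistical power of 0.8", "a significant level of 0.05" and an effect size of 0.35 that is not tied to any SF-36 score or visit.

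**The concern.** A reader cannot tell from the article which number decides the trial. PCS, MCS or any of eight subdomains could be presented as the primary result once the data are seen, and nothing in the text would contradict that. If any of them may succeed, a trial with no true effect has more than a 5% chance of appearing positive.

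The choice of score may well matter. The Discussion reports that systematic reviews "found a significantly improved PCS in the intradialytic exercise group, but not in the MCS", and then cites single subdomains that improved in individual studies. The stated aim of judging whether two sessions a week do about as well as three has the same problem: PCS and MCS could point in different directions, with no rule for which one governs.

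**Working it through.** **Inputs.** Three groups (section 2.2.2; equal allocation is assumed, as no ratio is given). Significance level 0.05, power 0.80, effect size 0.35 and N = 84 (section 2.5; 0.35 is read as Cohen's f, an assumption). Two component scores and eight subdomains (section 2.4.1). Follow-up at weeks 12 and 24 (abstract).

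**Step 1: reproduce 84.** For a one-way ANOVA with three groups, the noncentrality is λ = f²N = 0.35² × 84 = 0.1225 × 84 = 10.29, with 2 and 81 degrees of freedom. Power at 0.05 is 0.812, and 84 is the smallest multiple of 3 that reaches 0.80. So 84 is matched exactly by one three-group test of one variable.

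Section 2.5 names repeated measures ANOVA. Its between-group test over three measurements needs 57 patients at a correlation of 0.5, 69 at 0.7 and 72 at 0.8, and reaches 84 only at a correlation of 1. The alternative convention λ = f²N(m − 1) for the interaction gives 84 with m = 2 measurements, but that is the same calculation (λ = 10.29; 2 and 81 degrees of freedom). With m = 3 it gives 54. On either route to 84, the number pays for one test.

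**Step 2: false-positive chance under independence.** With k tests at 0.05 and no true effect, the chance of at least one significant result is 1 − 0.95^k:

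- k = 2: 1 − 0.9025 = 9.8%
- k = 4: 18.5%
- k = 8: 33.7%
- k = 16: 56.0%

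**Step 3: allow for correlation.** SF-36 scores and visits are correlated, so for most of these settings the independence figures are too high. Simulation used 10,000 null trials per setting, 28 patients per group and a one-way ANOVA at 0.05 on each variable. The documents give no correlations. Those assumed are 0 to 0.5 between PCS and MCS, 0.3 to 0.7 between subdomains, and 0.5 or 0.7 between visits.

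| What may count as primary | Visits | Tests | Independent | Simulated |
|---|---|---|---|---|
| One score | one | 1 | 5.0% | 5.0% |
| PCS and MCS | week 24 only | 2 | 9.8% | 8.7–10.2% |
| Eight subdomains | one | 8 | 33.7% | 20.4–30.4% |
| One score | both | 2 | 9.8% | 8.6–8.8% |
| PCS and MCS | both | 4 | 18.5% | 14.9–17.6% |
| Eight subdomains | both | 16 | 56.0% | 30.9–48.7% |

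The 10.2% slightly exceeds its independence value through simulation error only. The last three rows apply only if week 12 is tested as well.

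**Step 4: what an adjustment costs.** With PCS and MCS both primary at one visit and f = 0.35 for each, a test at 0.025 has power 0.724 with 84 patients, and 99 are needed for 0.80. Holm does slightly better than this, because a score may be tested at 0.05 once the other has passed at 0.025. Its power per score therefore lies between 0.724 and 0.812. All figures are before dropout.

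**The case against.** Several stronger readings are tempting, and the documents do not support them.

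- A reader might infer that the article claims a 5% error rate for the trial and breaks it. It does not. The 0.05 appears once, as an input to the sample size. No family-wise rate is claimed, and no level is stated for the analysis tests.
- A reader might take the wording in section 2.5 about every outcome variable as a plan to test each one at 0.05. That wording belongs to the Shapiro–Wilk normality check only.
- A reader might count at least four and up to sixteen primary tests. Section 2.5 places the group comparisons after the intervention, and section 2.3.2 has the exercise run for six months, so a single comparison at week 24 is a natural reading. A repeated measures test would also combine the visits. Measuring at week 12 is not the same as planning a primary test there.
- A reader might conclude that the document points to PCS. The link it draws between poor physical quality of life and mortality favours PCS, but the Discussion also stresses depression, low MCS in Taiwanese patients and the importance of mental health. The PCS and MCS contrast it reports comes from earlier reviews and is not a stated expectation for this trial.

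It can also be said that the article means one score, and that adjustment rules belong in a statistical analysis plan that is not shown. The ordering of secondary scores can indeed wait for that plan. Naming the primary variable cannot: the article has a section for it, and the single score it refers to is not among those it describes. None of these objections removes the multiplicity across scores at week 24.

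**Conclusion.** The point stands in a limited form. The primary outcome is an instrument that yields ten scores, no score or visit is fixed, and the sample size matches one test. The firmest figure is about 9–10% for PCS and MCS at week 24, against 5% for a single named score. It rises to about 20–30% if the eight subdomains may count at one visit. The figures of 15–18% and 31–49% hold only if week 12 is tested too.

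All of these assume that significance on any one score would be called a positive primary result, which the text neither states nor rules out. Their size depends on the assumed correlations, but the direction does not. Pairwise group comparisons and within-group tests are not counted.

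**What to change.** In section 2.4.1, name one SF-36 score at one visit as the primary variable. PCS at week 24, the end of the six-month programme, is one example, but the choice of score is the sponsor's. Make the other scores and the week-12 results secondary or exploratory.

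If both PCS and MCS are wanted, test them at week 24 with Holm and restate the power: about 0.72 per score with 84 patients at the 0.025 level, or 99 patients for 0.80 (15 more), before dropout.

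In section 2.5, state which variable and visit the sample size refers to. The sponsor should do so only after checking that the 0.35 effect size, taken from cited sources, applies to that variable and to the test that will be run.

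With one score at one visit, the cost is a sentence or so in each section plus that check, and 84 still gives power 0.812 if 0.35 applies. The downside is that a positive result on another score or at week 12 can no longer be called the primary result.
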